## Abstract

**Background:**

Care for people with dementia and their informal caregivers is a challenging aim in healthcare. There is an urgent need for cost-effective support programs that prevent informal caregivers of people with dementia from becoming overburdened, which might result in a delay or decrease of patient institutionalization. For this reason, we have developed the Systematic Care Program for Dementia (SCPD). The SCPD consists of an assessment of caregiver's sense of competence and suggestions on how to deal with competence deficiencies. The efficiency of the SCPD will be evaluated in our study.

**Methods and design:**

In our ongoing, cluster, randomized, single-blind, controlled trial, the participants in six mental health services in four regions of the Netherlands have been randomized per service. Professionals of the ambulatory mental health services (psychologists and social psychiatric nurses) have been randomly allocated to either the intervention group or the control group. The study population consists of community-dwelling people with dementia and their informal caregivers (patient-caregiver dyads) coming into the health service. The dyads have been clustered to the professionals. The primary outcome measure is the patient's admission to a nursing home or home for the elderly at 12 months of follow-up. This measure is the most important variable for estimating cost differences between the intervention group and the control group. The secondary outcome measure is the quality of the patient's and caregiver's lives.

**Discussion:**

A novelty in the SCPD is the pro-active and systematic approach. The focus on the caregiver's sense of competence is relevant to economical healthcare, since this sense of competence is an important determinant of delay of institutionalization of people with dementia. The SCPD might be able to facilitate this with a relatively small cost investment for caregivers' support, which could result in a major decrease in costs in the management of dementia. Implementation on a national level will be started if the SCPD proves to be efficient.

**Trial Registration:**

NCT00147693

## Background

Estimates state that the rapidly aging western European population will peak at about 2040 [1]. An aging population demands more healthcare and challenges the healthcare budget. Two-thirds of the people with dementia (also referred to as "patients" in this study protocol) are cared for at home [2]. Care at home is often intensive and burdensome. Informal caregivers of these patients carry a greater burden than informal caregivers of other chronically ill people [3], and they are at a greater risk of depression [4-6]. The institutionalized care of people with dementia is one of the three most expensive areas of healthcare [7,8]. Furthermore, as a result of the growing elderly population, shortages within institutional care are expected. The resulting budgetary constraint necessitates the exploration of temporary alternatives, such as postponement of institutionalization and care at home. Without unpaid informal caregivers, the costs of professional care at home would double [9]. Support is needed to prevent informal caregivers becoming overburdened and depressed. An informal caregiver's sense of being capable of giving care is a strong determinant of delaying institutionalization [10]. Contemporary policies have therefore been designed to shape conditions to support caring for people with dementia at home and to minimize the risk of depression for informal caregivers.

### Usual ambulatory mental healthcare

In the usual healthcare, in the Netherlands, the problems of informal caregivers often remain invisible until a crisis occurs. This happens partly because informal caregivers pay scant attention to their own problems, and professionals may not know how to support informal caregivers pro-actively [11]. When informal caregivers have become involved in care provided by the ambulatory mental health services (hereafter referred to as the "health services"), they are rarely screened in a structured manner for the problems they may encounter. There is, for example, no systematic screening for the care burden or depressive symptoms. Informal caregivers suffering from depressive symptoms are either treated inadequately or not at all [12,13]. Moreover, the available support of the health service varies from support groups for informal caregivers to case management for active support and organization of the care needed [14]. One of the reasons for this unsystematic care for informal caregivers is the lack of a national guideline for the health services for patients with dementia and the insufficient recognition of informal caregivers as part of the system surrounding these patients. This fragmented care is reflected in the different functions of the health services. The health services set their own standards for the care of patients and their caregivers. This service is provided in collaboration and concurrence with other regional providers.

### Effective support programs for caregivers of people with dementia

Usual care offers many opportunities to support informal caregivers that remain unused because of the late detection and the ad hoc identification and management of possible caregiver problems [12-15]. Several support programs for these caregivers have been developed, some of which have proven to be effective [16]. Most programs aim at reducing the caregiver's burden or enhancing feelings of competence in caring, and their purpose is to delay patient institutionalization. Dutch examples of these programs are the Family Support Program [17,18], the Meeting Centres Support Program [19], and the Community Occupational Therapy Intervention for patients with dementia and their informal caregivers [20,21]. These proven effective support programs found successively positive changes in caregiver depressive symptoms [22], patients' problem behavior and caregiver distress as related to patients' problem behavior [23-26], sense of competence and feelings of competence being a female caregiver sharing the same household with the patient [18,27], as compared to changes in the controls. Moreover, proven effective support programs found a positive influence of patients' severity of dementia on delay of nursing home placement, as compared to the control groups [28,29]. As part of the multicomponent intervention behavioral and cognitive strategies were used to train caregivers and patients in the use of aids to compensate for cognitive decline and to cope with distressing behavior. Caregiving intervention studies appeared effective in improving caregiver psychological health and quality of life [19,30-33] as well as patients' quality of life [34].

### The Systematic Care Program for Dementia

We have transformed the Family Support Program into a Systematic Care Program for Dementia (SCPD) that can be used in the first consultation of a professional with a patient and his/her informal caregiver (a patient-caregiver dyad) entering the health service. The SCPD consists of an assessment of the caregiver's sense of competence and suggestions on how to deal with competence deficiencies. The SCPD has been chosen because of its potential to help diagnose and treat problems systematically and to cover a wide range of individual problems. The SCPD is flexible in connecting pro-active interventions to individual problems. Moreover, it is also connected to the positive effects found in our previous study [18,35]. This program has been designed to fulfill the urgent need for effective and cost-effective support programs that can prevent overburdening the informal caregiver, which might result in a delay or decrease of patient institutionalization.

### Objectives

The objective of this study protocol is to describe the design of a trial to determine both the effectiveness and the efficiency of the SCPD in comparison to regular ambulatory mental healthcare. The aim of the program is to delay the institutionalization of the patient with dementia and to improve the health-related quality of life of both the patient and the informal caregiver.

### Hypothesis

We expect a delay of patient institutionalization in the intervention group as compared to controls at 12 months follow-up. In addition, we expect that time to institutionalization will be longer in the intervention group as compared to the control group.

## Methods and design

### Study design and setting

The study design is a single-blind, multicentre, cluster, randomized, controlled trial. From September 2005 to February 2006, the research assistant enlisted and randomized professionals (psychologists and social psychiatric nurses), initially from four health services, either to the intervention group or the control group. One service dropped out because of the interference with another clinical trial. In order to enroll patients in due time three other mental health care services were included. Altogether, professionals from six health services and four regions were randomized to either the intervention group or the control group. This setback in recruiting patient-caregiver dyads prolonged the inclusion period by 4 months to a total of 17 months. The follow-up period has been set at 1 year. One year proved long enough for us to find significant effects in our previous study [36]. Figure 1 presents the flow of the participants through the trial at each randomization procedure.

**Figure 1 F1:**
[figure not shown]
**Flow of the participants through the trial**.

The study cannot be double-blinded because all the professionals involved are aware of the treatment allocation. To prevent contamination, the intervention group have been asked to keep the study intervention secret and to inform neither professionals in the control group nor other colleagues nor field relations. The patient-caregiver dyads have been blinded to the group allocation of the professionals to whom they have been assigned. The intervention group will be trained to integrate the SCPD in their treatment method. Moreover, we assume that professionals will not be interested in telling patient-caregiver dyads that they are using a new or presumably better treatment method.

### Eligibility criteria

Health services were considered eligible if they could enroll clients with suspected dementia or with dementia. Furthermore, they had to be sure that they could recruit enough patient-caregiver dyads.

Professionals recruited by the health services were considered eligible if they treated at least four of the patient-caregiver dyads each year (see the section *Power calculations*). This is the minimum number required for reasons of continuity and routine. Moreover, this minimum is necessary so that the intervention professionals can change their daily routine and become familiar with the SCPD method.

The eligibility criteria for the dyads were:

1. The patient was referred to and entering the health service with the suspicion of dementia.

2. The patient lives in the community.

3. The patient has an informal caregiver living in the community.

4. The informal caregiver visits the patient at least twice a week.

5. The informal caregiver is willing to participate and gives written informed consent.

The exclusion criteria were:

1. The patient has no informal caregiver.

2. The informal caregiver is a client of the health service her/himself.

3. The informal caregiver is seriously ill and unable to participate in the study.

4. The informal caregiver does not speak Dutch fluently.

### Informed consent procedure

The informed consent procedure consisted of several steps. First, a psychologist or social psychiatric nurse provided written information for the informal caregiver. An informal caregiver who gave verbal consent and accepted the conditions was included in the next step. In this phase, the research assistant contacted the informal caregiver and made an appointment for the baseline interview, explained the assessment procedure, and answered questions. The informal caregiver was informed about the randomization procedure. After having given verbal consent, s/he received written confirmation of willingness to participate and the baseline questionnaire by post. An informal caregiver who was still willing to participate signed and returned the consent form and was included in the study.

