### Statistical analyses

Analyses will be performed at the level of the caregiver and the patient with dementia. All available data will be analyzed on an intention-to-treat basis, i.e. patient-caregiver dyads will remain in the group to which they are assigned. Descriptive analysis will be used to examine baseline comparability of both the intervention and control groups for sociodemographic characteristics, outcome parameters, and control variables. We will calculate the effect of the SCPD on the primary outcome measure (the number of institutionalizations) with Fisher's exact test. We will use multilevel logistic regression analyses to correct for the design effect of clustering patient-caregiver dyads with the professionals (level 1), and professionals in health services (level 2). We will use Kaplan-Meier survival analysis to quantify the effect of the SCPD on the primary outcome measure, time to institutionalization; and a Cox proportional hazard model, to correct for control variables. Analysis of the effect on the primary outcome and subgroup-analyses – adding the stratifying factor as a covariate and an interaction term of the stratifying factor with treatment group to the models – will be performed for shared household, age, and gender of the caregiver. Random coefficient regression analyses will be used to examine the effect of the SCPD on the secondary outcome measure (the quality of the patient's and the caregiver's lives) and also to correct for the clustering effect of the design, namely, patient-caregiver dyads clustered with professionals (level 1) and professionals in health services (level 2). We will also perform per protocol analyses. Mean substitution will be used for missing values unless at least if two third of the other items of that particular scale was completed. The software SPSS 16.0 (SPSS, Chicago, Illinois) and MLwiN Version 2.0 (Centre for Multilevel Modelling, University of Bristol, Bristol, UK) will be used for all statistical analyses.

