### Limitations

Although a strong study design was used, some design characteristics might interfere with the reliability and validity of future results.

First, two forms of inclusion bias may have occurred. The first is the services' method of recruiting professionals: professionals were free to decide whether they wanted to participate. This may mean that participating professionals are more interested in care for the caregivers than their average colleagues. They may be more motivated to learn, and they might perform better than their non-participating colleagues. It is possible that they already take better care of caregivers than their colleagues. In practice, however, this form of inclusion bias is limited because almost all the available professionals participated to generate the necessary number of professionals. The second form of inclusion bias concerns the willingness of patient-caregiver dyads to remain in the study until their end-point is reached. The informal caregiver's burden may be an influential predictor of their willingness to participate. It would be reasonable if caregivers with a great burden did not want to participate because they could not handle any more work. Analyses of caregiver nonparticipation might be useful.

Second, the possibility of contamination arising due to a change of contacts and a possible knowledge exchange between professionals in the intervention and control groups cannot theoretically be excluded. To overcome this problem in practice, any professionals allocated to the intervention group were emphatically asked to keep the study intervention secret and not to give information about the intervention to the professionals in the control group, other collogues, or field relations. To evaluate the success or failure of this request, the intervention group will be evaluated at each training session for such knowledge. They will be asked if they have been questioned about the training by colleagues and whether they were able to keep the secret.

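### Caregivers are first approached by clinicians who, on the natural reading, know their own allocation, and the institutionalization rate has no stated adjustment for baseline prognosis

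*Protocol article*

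**What the plan says.** Under Study design and setting, the professionals are the randomized units: "From September 2005 to February 2006, the research assistant enlisted and randomized professionals (psychologists and social psychiatric nurses), initially from four health services". Three further services joined after one dropped out, and this setback "prolonged the inclusion period by 4 months to a total of 17 months". The paragraph after Figure 1 explains why the trial is only single-blind: "The study cannot be double-blinded because all the professionals involved are aware of the treatment allocation".

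The Informed consent procedure begins with the clinician: "First, a psychologist or social psychiatric nurse provided written information for the informal caregiver". It goes on: "An informal caregiver who gave verbal consent and accepted the conditions was included in the next step". Only at that next step does the research assistant contact the caregiver.

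Under Statistical analyses: "We will calculate the effect of the SCPD on the primary outcome measure (the number of institutionalizations) with Fisher's exact test". A multilevel logistic regression follows, and clustering is the only purpose given for it. Control variables are attached to the Cox model for time to institutionalization. Shared household and the caregiver's age and gender enter as covariates with interaction terms, in a sentence about subgroup analyses. Baseline comparability is examined descriptively.

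The Limitations discuss professionals who volunteer and caregivers whose burden affects their willingness. On the latter they say: "Analyses of caregiver nonparticipation might be useful".

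**The concern.** Randomizing professionals balances the professionals. It balances their dyads only if enrolment of dyads is unaffected by knowledge of the arm. Here the clinician who opens the conversation can, on the natural reading, influence who hears about the study and how it is presented, while knowing which arm the dyad would join. One exclusion, a caregiver too ill to take part, leaves room for judgement. The programme can also start in the first consultation with screening of competence and depressive symptoms, whereas the Background says usual care does not screen systematically for burden or depressive symptoms. The two groups of professionals may therefore know different things about a caregiver at the moment of approach.

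If the arms enrol dyads of different prognosis, the difference passes directly into the institutionalization rate. It could look like a programme effect or hide one. Intention-to-treat analysis keeps enrolled dyads in their arm but cannot restore dyads who were never approached.

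**Working it through.** **1. Order of events.** The enlistment and randomization period given runs from September 2005 to February 2006, six months. Inclusion of dyads lasted 17 months, so at least 17 − 6 = 11 months lie outside that period. That dyads came in after their professional was randomized is the natural inference; the article does not state it as a rule.

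**2. Do the stated safeguards reach the first approach?**
- Dyads are blinded to their professional's group. This limits the caregiver's own reaction to the arm, not the clinician's choice or manner of approach.
- The research assistant is said not to know the assignment, but enters only after the caregiver has agreed verbally.
- Intention-to-treat applies after enrolment.
- The Limitations cover volunteering professionals, burdened caregivers, contamination and performance bias. None of these is recruitment of dyads that differs by arm.

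**3. Which comparison carries the sample size?** The Power calculations use 28% and 14%, 80% power, two-sided 0.05. With pooled variance under the null and no continuity correction:

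n = [1.960 × √(2 × 0.21 × 0.79) + 0.842 × √(0.28 × 0.72 + 0.14 × 0.86)]² / 0.14² = 131.7, so 132 per arm, as stated.

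Design effect 1 + (4 − 1) × 0.05 = 1.15, and 132 × 1.15 = 151.8, so 152, as stated. The trial is thus sized on the comparison of rates, for which no prognostic adjustment is described.

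**4. How large could the bias be?** The documents give no figure for this. The following is an illustration under assumptions: no programme effect, overall risk 28%, half of the dyads high-risk, a high-to-low risk ratio R of 2 or 3, 152 analysed per arm, clustering ignored. The share of high-risk dyads is s lower in the intervention arm.

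Low risk = 0.28 / (0.5 + 0.5R): 0.1867 for R = 2 and 0.14 for R = 3. High minus low = low × (R − 1): 0.1867 and 0.28. Spurious difference = s × (high − low). The last column is the exact two-sided Fisher rejection probability.

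| R | s | Spurious difference | Rejection with no effect |
|---|---|---|---|
| either | 0 | 0 | 3.7% |
| 2 | 0.10 | 0.10 × 0.1867 = 1.9 points | 5.0% |
| 2 | 0.20 | 0.20 × 0.1867 = 3.7 points | 8.9% |
| 3 | 0.10 | 0.10 × 0.28 = 2.8 points | 6.6% |
| 3 | 0.20 | 0.20 × 0.28 = 5.6 points | 16.0% |

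A second set of assumptions gives a similar range. Let 40% of dyads be high-burden with risk 45%; the rest then have (0.28 − 0.40 × 0.45) / 0.60 = 16.7%. If the intervention arm enrols 30% high-burden dyads, its rate is 0.30 × 0.45 + 0.70 × 0.167 = 25.2%, a spurious 2.8 points. At 20% it is 0.20 × 0.45 + 0.80 × 0.167 = 22.3%, a spurious 5.7 points. Against the planned 14 these are 20% and 40%.

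**The case against.** Several parts of the opposing case are right and limit the point.

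- A reader might infer that each dyad was chosen by its own randomized professional. The article does not say so. It names a psychologist or nurse, does not describe how dyads are assigned to professionals, and the flow figure is not available here. The matching job titles, and a programme that can begin in the first consultation, make this the natural reading, no more.
- A reader might infer that the primary analysis has no prognostic adjustment, or that Fisher's test alone decides the trial. Neither is supported. Rate and time to institutionalization are both taken as primary without ranking, and time has a Cox model with control variables. Three caregiver or household factors also enter primary-outcome models, but as subgroup terms.
- A reader might count the suspicion of dementia as an elastic criterion in the professional's hands. It attaches to referral and entry to the service, so it does not carry the argument.
- A separate analysis plan might give the logistic model covariates. That is possible, but this article states a purpose for the model, and the purpose is clustering.
- Adjustment cannot remove selection on unmeasured factors. This is true, and it is why the result must be reported with that caveat.
- Adjusting for every baseline score could do harm: the posted baseline questionnaire follows the clinician's approach, so the sense-of-competence and depression scores may already reflect programme contact. This also stands, and it shortens the covariate list.

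**Conclusion.** The point holds in a limited form. Professionals who know their arm probably make the first approach to caregivers, nothing described prevents the enrolled dyads from differing by arm, and the comparison on which the trial was sized has no stated adjustment for prognosis.

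The article shows that bias is possible. It does not show that bias occurred, in which direction, or how large it is, so a conclusion that the result will favour the programme would go too far. Under the assumed imbalances of 10 to 20 points in high-risk dyads, the spurious difference is roughly 2 to 6 percentage points against the planned 14. That range depends wholly on the assumed risk split and imbalance, and the rejection probabilities also ignore clustering.

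**What to change.** Recruitment is described in the past tense, so the remedy lies in analysis and reporting. It should be fixed before the arms are compared.

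1. Make the main estimate for the institutionalization rate the multilevel logistic model, with dyads within professionals within health services, adjusted for baseline factors in Table 1 that the programme cannot have changed: patient age and gender, caregiver age and gender, relation to the patient, and shared household. Report the unadjusted result as supportive.
2. Use the baseline NPI-Q, SCQ and CES-D scores and dementia severity only in a sensitivity analysis. The scores may follow programme contact, and severity is described as the observation of professionals, who know their arm.
3. Where service records allow, report approach and consent by arm. The article does not say what records exist, so this cannot be promised.
4. State that adjustment removes only measured imbalance and that the size and direction of any remaining bias are unknown.

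The cost of the first two items is wording in the analysis plan, with no new data. The downsides are a few dyads with missing covariates, who need a stated rule, and an odds ratio that is conditional on the covariates and clusters.
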